## 2.2 Background

The national incidence of PTH ranges from 2.6% to 10% and presentation varies from mildly darkened oral secretions to active hemoptysis^11,12^. However, the incidence may be under-reported, because most of these studies are retrospective with varying criteria for what constitutes a PTH. Additionally, ED studies report high rates of re-bleeding in patients that previously presented with a normal exam or stable clot^5^. Current non-operative PTH interventions, including hemostatic drugs, blood products, or topical agents have failed to prevent the need to return to the operating room and its associated risks^4^. Our first retrospective cohort document that three doses of nebulized tranexamic acid delivered for PTH appear to be safe and beneficial in a 44% reduction in the need for an operation to re-establish hemostasis^13^. Despite earlier reports that intravenous TXA increases the seizure risk in pediatric patients, no reports document that topical or local delivery of TXA causes adverse reactions^14^.

Non-operative control of airway and upper GI tract bleeding is of keen interest to pediatric surgeons, emergency, and intensive care unit health care providers. There is clear evidence that general anesthesia in children increases the risk of neurotoxicity, suggesting a need to avoid surgical management of PTH when safely possible^15^. Therefore, proven interventions that reduce operating room exposure would reduce morbidity and mortality. Systemic administration of TXA achieves hemostasis both intra- and post-operatively in orthopedic, dental, cardiovascular, and trauma literature^16^. However, systematic reviews document that intravenous TXA may not be effective when administered prophylactically or perioperatively to prevent PTH^17^. Additionally, large retrospective studies document that intravenous TXA can have significant delayed-onset adverse events including an increase in seizures, thromboembolic events, renal insufficiency, and changes in vision^14^.

Systemic administration of TXA achieves hemostasis both intra- and post-operatively in orthopedic, dental, cardiovascular, and trauma literature (19, 20). Systematic reviews document that intravenous TXA may be effective when administered prophylactically or perioperatively to prevent primary PTH but not secondary PTH (21). Additionally, large retrospective studies document that high-dose intravenous TXA can have significant delayed-onset adverse events, including seizures, thromboembolism, renal insufficiency, and changes in vision (17). Given the potential risks associated with systemic TXA administration, oral inhalation of TXA may have fewer side effects and be more effective. Studies document that inhaled drug formulations compared to intravenous increase airway and upper GI tract tissue exposure (22). Schwarz *et al.* was the first to report a case of a three-year-old boy to receive nebulized TXA who presented on postoperative day three with a PTH (23). The patient did return to the operating room, but the bleeding had stopped on arrival thus no operative intervention was needed. In 2021, we published a retrospective cohort documenting that three doses of nebulized tranexamic acid delivered for PTH in children appear to be safe and beneficial. This study documented a 44% reduction in the need for a second operation (24). Compared to earlier reports and studies, nebulized TXA is the first non-operative intervention that successfully decreased the need for an invasive procedure to control upper airway bleeding in children with PTH. This study was supported with a larger retrospective study of 83 patients treated, documenting a significant decrease in the need for operative control and repeat bleeding (25). Shin *et al* reported that TXA-treated patients had a decreased rate of operating room intervention of 36.1% versus 60.2% (p<0.0001) and a rate of repeat bleeding of 4.9% versus 14.2% (p<0.02). The odds ratio for operating room intervention with TXA treatment was 0.37 (95% CI 0.22, 0.63). There were no adverse effects identified with an average follow-up time of 586 days.

Nebulization of TXA is not a common route of administration compared to oral or intravenous delivery. Inhaled or intranasal medication can be rapidly absorbed across the large surface area of the respiratory tract epithelium. Some drugs absorbed into the pulmonary circulation enter directly into the systemic circulation via the pulmonary vein, possibly bypassing first-pass metabolism that occurs with oral drugs. Previous research into the site of action for inhaled medications has been limited to animal studies because biopsy of the entry site would be dangerous to the subject. However, to choose the optimal dose it is important for investigators to understand the level of absorption at the topical and systematic level. Typical pharmacokinetics of TXA cannot be done in this study, however the concentrations can be estimated by verifying physiologically based pharmacokinetic (PBPK) model designed to predict the change in pharmacokinetics that occur as the inhaled drug cross the respiratory epithelium. A pulmonary PBPK model begins with extracting from the literature all known pharmacokinetic data on the inhaled drug and the known properties for absorption and metabolism across the respiratory epithelium. Fortunately, several pharmacokinetic studies using healthy adults or animals have been performed with TXA. Additionally, several pediatric and inhaled pharmacokinetic studies are available. Utilizing this data, we can build a PBPK model to predict the level of topical and systematic absorption. The main advantage of this method is to understand how an inhaled drug is absorbed and metabolized in the respiratory epithelium with the fewest number of systematic samples. Instead of collecting a wide range of samples from different ages and doses, we only need a few samples to verify that the parameters used to build the model were correct. This technique has been used in multiple studies to predict the dosing response in various populations or using different routes of administration.

## 2.3 Risk/Benefit Assessment

### 2.3.1 Known Potential Risks

The known potential risk to the study will be minimized to include three categories:

A. Immediate Risk would include continued blood loss leading to worsening hemodynamic instability or airway loss. However, the study will not interfere with routine post-tonsillectomy hemorrhage care, therefore the risk of uncontrolled hemorrhage will be minimized.

B. Long Term Risk: The major long-term risk is from study design as a pilot study may not detect safety outcomes due to the small sample size. Another possible long-term risk is from toxicity from tranexamic acid organized into three categories:

1. Common but not harmful: headache, abdominal pain, oral, back, or muscle pain, or sinus congestion

2. Rare and serious: severe depression, allergic reaction, vision changes, seizures, thrombotic events, or ureteral obstruction

3. Rare but important or life-threatening: allergic skin reaction, anaphylaxis, cerebral thrombosis, achromatopsia, conjunctivitis (ligneous), deep vein thrombosis, diarrhea, dizziness, hypersensitivity reaction, hypotension (with rapid IV injection), nausea, pulmonary embolism, renal cortical necrosis, retinal artery occlusion, retinal vein occlusion, seizure, ureteral obstruction, visual disturbance, or vomiting.

C. Alternative Procedures: Current literature does not contain an established and effective non-invasive intervention for post-tonsillectomy hemorrhage. Non-operative management for active PTH includes conventional techniques such as direct pressure, clot suction, silver nitrate, and thrombin powder^4^.  The American Academy of Otolaryngology Surgery guidelines does not recommend any of these therapies because none have decreased the need for reoperation^18^. A double-blind randomized trial examined intravenous tranexamic acid delivered during pediatric adenoid-tonsillectomy, this study documented no decrease in perioperative blood loss or incidence of secondary bleeding. After this study, a meta-analysis was performed documenting a significant decrease in blood loss but did not find any change in post-tonsillectomy hemorrhage^19^.

### 2.3.2 Known Potential Benefits

The study's primary outcome is the need to go back to the operating room for hemostatic control within 24 hours from randomization. Although repeat surgery can restore hemostasis for post-tonsillectomy hemorrhage, it is not a guarantee of success. One small study of nonactive bleeding patients documented that the rate of rebleeding was 26/203 (12.8%) after inpatient observation and 3/21 (14.3%) after an operative intervention^5^. Our review of studies has revealed a modestly increased risk of adverse neurodevelopmental outcomes in children exposed to a single episode of general anesthesia and compounds with multiple exposures^15^.  Therefore, a reduction in exposure to a second surgery involving cauterization, anesthesia, and anxiety would significantly benefit children with post-tonsillectomy hemorrhage. Moreover, research into non-operative interventions will help future children who suffer from aerodigestive bleeding.  The benefits can be further classified into two groups:

A. **Immediate Potential Benefits**

1. Prevention of the need to return to the operating room for cauterization

2. Decrease in acute pain and anxiety in avoiding a procedure.

B. **Long-term benefits**

1. Reduction in anesthesia exposure may improve neurodevelopmental outcomes.
2. Avoidance of secondary procedure may improve early return to normal activities and improved quality of life in terms of benefits of the initial tonsillectomy including reduction of tonsillitis and sleep apnea symptoms.
3. The pilot study will inform an improved study design for a larger trial.
4. The pilot study will verify a PBPK model that will provide useful information on dosing and absorption of the nebulized TXA.

### 2.3.3 Assessment of Potential Risks and Benefits

Children with PTH typically do not receive hemostatic interventions in the ED while awaiting the otolaryngologist’s arrival. Also, many children with PTH present to hospitals that do not have immediate access to pediatric otolaryngology and thus require transport to tertiary hospitals. Nebulized TXA has the potential to be an easy, efficient, and safe ED intervention to stabilize potentially life-threatening bleeding from PTH and decrease the need for surgical intervention. Pilot trials in children designed with full-scale procedures help assess the feasibility and safety of large multi-center phase 3 trials. A smaller pilot trial can give go/no go information to progress to a larger phase 3 trial while minimizing the risks to the population. Additionally, starting with three doses of TXA may reduce the need for re-operation, further increasing the benefits of the study.  Determining the local (indirect estimate) and systematic (direct measurement) concentrations of nebulized TXA will help to choose an optimal dose for the larger trial. PTH is the leading cause of mortality in the second most often performed surgical procedure in children. Developing an effective, non-invasive, low-risk solution would benefit public health by addressing the life-threatening complications PTH in children.  

# 3 Objectives and Endpoints

| OBJECTIVES | ENDPOINTS | JUSTIFICATION FOR ENDPOINTS |
| --- | --- | --- |
| Primary | | |
| Evaluate the feasibility to enroll 0.6 patients/site/month  Nebulize at least two of three doses of TXA to children with PTH.  Determine the local and systematic concentrations of nebulized TXA in children  Determine incidence of adverse and serious adverse events | Enrollment after one year and % of nebulization’s. Go/no-go threshold is 0.6 patients per site per month for a total of 22 patients. Time and success to obtain consent will establish need for exception for informed consent (EFIC).    The goal is >90% of patients will receive at least two of three planned nebulization of TXA.  Collection of two blood samples from each participant. This will verify a pulmonary physiological-based PK model (PBPK) (i.e., nasal cavity, pharynx, and lung) that indirectly predicts the oropharyngeal and systematic concentration of nebulized TXA.  A phone call or email will be placed to participants at 30 +/- 5 days. | The overall incidence of PTH is 5%, yet numbers per site may be very different. Assessment and consent will optimize site selection, recruitment process, and the plan the main trial.    The establishment of a pragmatic protocol design will help design a large trial.  Limited data on nebulized TXA systematic absorption. Topical PK studies of TXA document a significant reduction in systematic levels but the same hemostasis effect.  Safety Evaluation as recommended by the FDA. |
| Secondary | | |
| Determine the number and rationale for PTH patients to return to the OR; and    Determine the number of blood transfusions and estimated blood loss and      Determine the recurrence of PTH after TXA, saline, or return to the OR. | Collection number participants and surveys on ENT surgeons’ decision to go to the OR    Collection of electronic health record data on number of blood transfusions and estimated blood loss    Survey families to determine PTH recurred seven days from randomization. | To evaluate if return to the OR can be an outcome for the main trial.    To evaluate if TXA decreased severity of PTH bleeding.      To evaluate if TXA or return to OR prevented PTH recurrence. |
| Tertiary/Exploratory | | |
| Establish pain and anxiety after receiving study intervention. | Age-appropriate pain and anxiety state (PROMIS) at 7 +/- 1 days after randomization. | Surgical procedures provoke significant parental and child anxiety. Reduction in parent and child anxiety is a strong patient-centered outcome of quality care. |

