## 5.5 Strategies for Recruitment and Retention

The pilot study aims to test the feasibility of enrolling 0.6 patients per site per month. The specific goal for this pilot trial is to enroll 12 patients (6 treatment groups & 6 control group) at the University of Texas Health Science Center (UTHSCSA)/University Hospital in San Antonio, TX. The participants will be children who present to the emergency department (ED) with secondary posttonsillectomy hemorrhage (PTH) occurring 24 hours or more after their tonsillectomy. PTH patients will be screened and approached in the ED. Participants will be followed as outpatients for one week post-randomization. Due to the short follow-up period, we do not expect a significant loss of participants. However, text, phone, and e-mail information will be obtained from each participant to give the study team multiple options for gathering data on secondary and tertiary objectives. In this pilot analysis, we will offer participants an incentive to complete all study procedures. We will also closely monitor study completion to determine if participant incentives are necessary for the main trial. This pilot study will help assess the feasibility of enrollment rates and the effectiveness of follow up methods, which will inform the design and implementation of the larger main trial.

The investigators will enroll at the University of Texas Health Science Center (UTHSCSA)/University Hospital in San Antonio, TX for the single site and the multi-site study, the University of California at Davis Medical Center in Davis, CA, and Hasbro Children’s Hospital in Providence, RI. Each of the ENT and ED colleagues at each site have provided the incidence of PTH, percentage that return to the OR, and the monthly ED visit rate. Previous studies document that PTH primarily presents at night, therefore we arrange for 24/7 coverage at each site.

| **Site** | **Annual PTH Incidence** | **Going to OR** | **Monthly ED Visits** |
| --- | --- | --- | --- |
| San Antonio, TX | 5.4% | 73% | 1.60 |
| Davis, CA | 3.2% | 70% | 0.63 |
| Providence, RI | 2.8% | 63% | 2.80 |

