## 9.2 Sample Size Determination

Multiple studies suggest that 76% of children with PTH go to the OR for surgical control of their hemorrhage. This pilot study sample size is based on the goals for the subsequent phase 3 trial. Conservatively, we estimate that nebulized TXA will decrease the incidence of surgical care for PTH from 76% to 61%, or in other words a 15% effect size.  The sample size for phase 3 trial based on an effect size of 0.15 with randomization of 324 children with PTH using an a priori, one-tailed, Fishers exact test stratified by site, with 80% power, alpha=0.025. This trial will then need to enroll at least 0.6 patients per site per month at 12 sites over 4 years (0.563 patients x 12 sites x 48 months = 345 patients). Thus, the go/no-go threshold for the subsequent phase 3 trial is an enrollment goal of 0.6 patients per site per month in this pilot study. For the single site trial designed for one year, we hope to enroll 12 patients. For the mutli-site study we hope to enroll 22 patients’ across 3 enrolling sites over 12 months at 0.6 patients x 3 sites x 12 months = 21.6, rounded up to 22 targeted enrollments.

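### The go/no-go count of 22 mixes the fraction of children enrolled with the visit volumes of three pilot sites, and no condition ties those volumes to the twelve phase 3 sites

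*Protocol*

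**What the plan says.** Section 3 (Objectives and Endpoints) sets the rule: "Go/no-go threshold is 0.6 patients per site per month for a total of 22 patients". Section 9.2 derives the count as "0.6 patients x 3 sites x 12 months = 21.6, rounded up to 22 targeted enrollments". It takes the rate from phase 3: "This trial will then need to enroll at least 0.6 patients per site per month at 12 sites over 4 years". The pilot rate is then named as the threshold for going on to that trial.

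Section 5.5 says that colleagues at each site "have provided the incidence of PTH, percentage that return to the OR, and the monthly ED visit rate". Its table has three rows, the last column being monthly ED visits:

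- "San Antonio, TX | 5.4% | 73% | 1.60"
- "Davis, CA | 3.2% | 70% | 0.63"
- "Providence, RI | 2.8% | 63% | 2.80"

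Beside the rule, section 3 accepts that case numbers may vary greatly between sites and expects the pilot to inform site selection. It also assesses the time and success of consent, tied to whether an exception from informed consent is needed. Sections 5.4 and 6.4 collect eligible children who were not enrolled. None of this enters the go/no-go, and no visit volume is stated for the phase 3 sites.

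**The concern.** Enrollment per site is visit volume times the fraction of visits enrolled. The volume belongs to the sites chosen for the pilot. The fraction says something about consent, coverage and workflow, and is the part with a better claim to carry over to new sites. A single pooled count does not separate the two.

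The pilot volumes differ by a factor of more than four (2.80 / 0.63 = 4.4), and one site holds over half the visits. The same passing count could therefore come before a phase 3 trial that recruits comfortably or one that falls far short, depending on which twelve sites are picked. The rule as written gives no warning of the second case. At stake is the main decision that the pilot exists to support.

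**Working it through.** **Inputs.** Monthly visits of 1.60, 0.63 and 2.80 (section 5.5); 0.6 per site per month, 3 sites, 12 months, and 12 phase 3 sites for 48 months (section 9.2); phase 3 sample size 324 (section 9.2). My assumptions: the visit column counts visits for post-tonsillectomy hemorrhage, and one fraction *f* is enrolled at every site.

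**The plan's own figures.** 0.6 × 3 × 12 = 21.6, rounded up to 22: reproduced. The 324 also reproduces: a one-sided Fisher exact test at 0.025, 76% against 61%, 162 per arm, has exact power 0.801. The phase 3 accrual line does not: it reads "0.563 patients x 12 sites x 48 months = 345 patients", but 0.563 × 12 × 48 = 324.3, while 0.6 × 12 × 48 = 345.6. I use 324 as the requirement, the more lenient of the two.

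**Fraction that just gives 22.** Total volume is 1.60 + 0.63 + 2.80 = 5.03 per month, or 60.36 per year. Shares are San Antonio 32%, Davis 13% and Providence 56%. The fraction is *f* = 22 / 60.36 = 0.364.

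**What that fraction means by site.** Phase 3 yield = volume × 0.3645 × 12 sites × 48 months (576 site-months).

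| Volume like | Visits/month | Enrolled/month at *f* | Fraction needed for 0.6 | Phase 3 yield |
| --- | --- | --- | --- | --- |
| Providence | 2.80 | 1.02 | 0.6/2.80 = 21% | 588 |
| San Antonio | 1.60 | 0.58 | 0.6/1.60 = 38% | 336 |
| Davis | 0.63 | 0.23 | 0.6/0.63 = 95% | 132 |
| Three-site mean | 1.68 | 0.61 | 0.6/1.68 = 36% | 352 |
| Mean of San Antonio and Davis | 1.12 | 0.41 | 0.6/1.12 = 54% | 234 |

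**Volume that phase 3 needs at this fraction.** For 0.6 per site per month: 0.6 / 0.3645 = 1.65 visits. For 324 exactly: (324 / 576) / 0.3645 = 1.54. The pilot mean of 1.68 just clears both; without Providence the mean of 1.12 clears neither. A bare pass therefore supports phase 3 only if its sites are, on average, about as busy as the pilot sites.

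**Does the rule respond to recruitment?** With Poisson enrollment over 12 months, P(go) = P(Poisson(60.36 *f*) ≥ 22). This gives 0.006 at *f* = 20%, 0.21 at 30%, 0.53 at 36.4%, 0.70 at 40% and 0.95 at 50%. It does, and steeply.

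**Precision of the proposed fraction.** As an illustration, 22 enrolled of 60 eligible is 0.367, with an exact (Clopper-Pearson) 95% interval of 0.25 to 0.50. The implied minimum volume is 0.6 / 0.367 = 1.64, with limits 0.6 / 0.50 = 1.20 and 0.6 / 0.246 = 2.44. At a single small site, 4 of 8 has an interval of 0.16 to 0.84, too wide to act on.

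**The case against.** The best defense is that phase 3 needs an average, not a minimum at each site. Section 9.2 multiplies a rate by sites and months to reach a total, and builds the pilot's 22 in the same way, so pooling is the matching scale. That stands. The threshold is also well placed for the pilot's own site mix: at the three-site mean, 324 patients need (324 / 576) / 1.677 = 33.5% enrolled, and the rule asks for 36.4%.

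Two stronger readings are tempting, and the document supports neither.

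- A reader might infer that the rule fails because Davis could hardly reach 0.6 a month. But neither section 3 nor section 9.2 requires 0.6 at every site, so a shortfall at one site is not a failure of the rule.
- A reader might infer that go reflects only how many cases the chosen sites see. The probabilities above refute this: at fixed volumes, P(go) runs from 0.006 to 0.95 as the fraction rises from 20% to 50%.

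It is also fair to say that twelve sites as small as Davis is an extreme nobody proposes, and that at 50% enrolled the pilot-average volume would yield 0.5 × 1.677 × 576 = 483 patients, well above 324. Finally, section 3 already recognizes variation between sites, and the missed-eligible data are planned. What remains is that none of this is attached to the decision. The rule is fixed in the protocol itself, so this is more than a reporting detail left to an analysis plan.

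**Conclusion.** The point holds as a limited one. The count of 22 is correctly calculated and pooling is appropriate, but the count alone cannot support a phase 3 go, because it carries an unstated condition that the phase 3 sites average about the pilot's volume. At a bare pass, the projected phase 3 yield is 352 patients at the pilot mean, 336 at San Antonio volume, 234 at the San Antonio and Davis average, and 132 at Davis volume, against 324. The document does not show that phase 3 would fall short; it leaves open which of these applies.

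The figures rest on reading the visit column as hemorrhage visits, on a common fraction enrolled, and on a 12-month pilot. Section 9.1 gives 18 months for the multi-site study; 22 patients in 54 site-months is only 0.41 per site per month, so the period must be settled before the count means anything fixed. This is a cheap improvement to a decision rule, not a flaw that stops the pilot.

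**What to change.** In sections 3 and 9.2, keep the 0.6 threshold and add:

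1. The fraction enrolled / (enrolled + missed eligible), pooled over sites with an exact confidence interval, and shown by site for description only, since site-level intervals will be wide.
2. A condition on go: the planned phase 3 sites' mean eligible visits per site per month must be at least 0.6 divided by the pooled fraction. Report the same quotient at both confidence limits.
3. A sentence that 22 pooled does not imply that each site reached 0.6, noting that Davis would need about 95% of its visits.
4. One stated enrollment period for the multi-site count, and a definition of the visit column in section 5.5.

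The cost is wording and one table. No patients or procedures are added: sections 5.4 and 6.4 already collect missed-eligible children, and the limit of 100 records per site exceeds even Providence's expected 2.80 × 12 = 34 visits a year. The price is that go becomes conditional on phase 3 site volume and carries the imprecision of the estimated fraction. That a fraction from three sites carries over to others remains an assumption, and should be stated as one.
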